#### Exclusion criteria

History of head or eye injury or epilepsy.Body metallic implants, pacemaker, claustrophobia and any other contraindication to fMRI or rTMS.Current use of psychotropic drugs (except for antidepressants on a stable dose for at least one month).Current use of any anti-obesity drug (e.g. sibutramine, orlistat) and medications that are known to reduce weight, such as Liraglutide and Topiramate (three months washout period for any medication).Pregnant or breastfeeding.Diabetes Mellitus diagnosis.Major psychiatric disorder requiring immediate treatment (e.g. Schizophrenia, Bipolar Disorder).Substance dependence (smokers of less than 5 cigarettes/day will be included).Individuals currently receiving any psychological therapy for ED.Cushing’s and Turner’s syndrome.

*Control participants will be excluded if they meet psychiatric disorder criteria based on the MINI International Neuropsychiatric Interview 7.0 [57].

#### Withdrawal criteria

Participants will be withdrawn from the study if they: i) become pregnant; ii) experience any adverse event which the study investigator specifies as an indicator that it is no longer safe for the individual to participate; iii) initiate the use of any medication described as an exclusion criteria; iv) develop psychotic or manic symptoms, or v) failure to complete three consecutive rTMS sessions.

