### Intervention

Following assessment, participants eligible for the study will undergo a preliminary fMRI, followed by 20 sessions of neuronavigated rTMS, one session per day, 3 days/week over approximately 7 weeks. Focal rTMS will be performed using a Neurosoft device and a ‘figure of eight’ coil. Brainscience Neuronavigation will be used to guide the placement of the coil to the target PFC region using a template MRI for all participants. The coil will be placed at a 45° angle to the mid-sagittal line to induce a posterior to anterior current in the underlying neural tissue. For the real treatment condition, stimulation will target the left DLPFC at 110 % of the resting motor threshold. Each session of 10 Hz stimulation will apply 1000 pulses to the left hemisphere, with a duty cycle of 5 s on and 55 s off, for a total stimulation time of 20 min. Sham rTMS treatment will be administered with the same TMS methodology used for real intervention, except for the fact that in the sham condition there is no actual magnetic stimulation. In order to mimic the cutaneous sensation and muscle twitching of rTMS without stimulating the brain, focal electrical stimulation will be used as a sham rTMS condition. To ensure treatment adherence, if rTMS sessions are missed, replacement sessions will be schedule within a week.

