### Sample size and statistical analysis

To detect the change in craving and BE frequency before and after treatment intervention, the following parameters were used to estimate sample size: effect size *f* = 0.31 (supposed to be small), alpha error probability =0.05, power = (1-β error probability) = 0.8, number of groups = 2, number of measurements through the follow-up = 3 and correlation among repeated measurements = 0.5.

Statistical Inferences: Two different types of analyses will be used to evaluate the effectiveness of the rTMS. The first (and standard) method is intention-to-treat (ITT) that assumes that every patient allocated to be intervention actually received it [75]. The other paradigm, CACE estimation method [76, 77] will take into account the compliance status (patient’s adherence to the rTMS).The compliance status is defined here as at least one of 20 session of rTMS; CACE estimation, therefore, provides a realistic effect under non-adherence phenomenon being estimated based on the structural equation modeling. Underlying both paradigms, it will be used growth modeling, which examines the development of individuals on one more outcome variables over the time. In growth modeling (on contrary of repeated ANOVAS), random effects are used to capture individual differences in development. The corrected significance level (Bonferroni) to be adopted due to 32 outcomes will be 0,0015. Such procedure will be carried to avoid false discovered rate due to multiple comparisons. All the statistical inference will be done via Mplus 7.0. In addition, careful fMRI image acquisition and processing will be completed and analyzed taking into consideration the limitations of fMRI studies.

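### The withdrawal rule takes participants out of the study, not only off rTMS, and the article says nowhere that their T.23 and T.24 outcomes, which the ITT and CACE analyses need, are still collected

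*Protocol article*

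**What the plan says.** The Withdrawal criteria section begins "Participants will be withdrawn from the study if they" and gives five triggers. Three matter most here:

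- adherence: "failure to complete three consecutive rTMS sessions";
- a new treatment: "initiate the use of any medication described as an exclusion criteria";
- harm, limited to participants who "experience any adverse event which the study investigator specifies as an indicator that it is no longer safe for the individual to participate".

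The other two are pregnancy and psychotic or manic symptoms. The Intervention section eases the adherence trigger: "if rTMS sessions are missed, replacement sessions will be schedule within a week".

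Under Primary outcome measures, the binge-eating outcome is the change in diary-recorded episodes from T.3 to T.23. Under Secondary outcome measures, that diary covers the 15 days before T.3, T.23 and T.24 only. The Abstract adds that binge episodes are also assessed at each treatment session.

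The Sample size and statistical analysis section promises two analyses, both by random-effects growth modelling. The first is "intention-to-treat (ITT) that assumes that every patient allocated to be intervention actually received it". The second is CACE, which it says "provides a realistic effect under non-adherence phenomenon". For CACE, a participant complies by attending one or more of the 20 sessions.

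**The concern.** Stopping a treatment and leaving a trial are different events. An intention-to-treat comparison needs outcomes from those who stopped as well as those who continued. The rule as printed joins the two, and its triggers are tied to adherence, to seeking other treatment and to tolerability. These can plausibly differ between arms: a sham participant with no benefit may stop attending or start a weight-reducing drug, while an active participant may stop because of side effects.

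If outcomes end at withdrawal, the primary comparison has gaps created by events after randomisation, and the randomised allocation no longer protects it in full. The follow-up hypothesis at 8 weeks has the same exposure. No analysis plan can recover outcomes that were never collected.

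The printed ITT definition does not help. ITT makes no assumption that treatment was received; it analyses people in the arm to which they were randomised, whatever they received.

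**Working it through.** **1. The passages side by side**

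| Participant | Result under the withdrawal rule as written | Status in the promised analyses |
|---|---|---|
| Withdrawn after one or more sessions | Baseline diary and session counts up to withdrawal; no T.23 or T.24 diary | In ITT without a primary change score; a complier for CACE |
| Attends no session | Meets the three-consecutive-session trigger unless replacement sessions are attended; baseline only | In ITT without a primary change score; the only kind of non-complier for CACE, with no outcome |
| Completes treatment | T.3, T.23 and T.24 | In both analyses |

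The second row is the sharpest conflict: CACE has to model non-compliers, and the rule removes them before any outcome is taken.

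**2. Reproducing the sample size**

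Inputs from the sample size paragraph: f = 0.31, alpha 0.05, power 0.80, 2 groups, m = 3 measurements, correlation 0.5. The total of 60 is in the overview of the design.

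For the between-groups F test, λ = f² × N × m / (1 + (m − 1) × 0.5), with 1 and N − 2 degrees of freedom. Here m / (1 + 2 × 0.5) = 1.5 and f² = 0.0961, so λ = 0.0961 × 1.5 × N.

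- N = 58: λ = 8.36, power 0.811 (the smallest even N reaching 0.80).
- N = 60: λ = 8.65, power 0.824.

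The stated 60 is therefore reproduced, with a reserve of about 2 participants. The within-subject and group-by-time versions both give N = 20, so they are not the source of 60.

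**3. Power if withdrawn participants contribute nothing**

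The documents give no withdrawal rate, so a range is assumed.

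| Loss | N left | λ | Power |
|---|---|---|---|
| 10% | 54 | 7.78 | 0.782 |
| 20% | 48 | 6.92 | 0.731 |
| 30% | 42 | 6.05 | 0.670 |

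**4. Bias of an observed-case contrast**

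Let w be the proportion withdrawn in an arm, and let withdrawn participants' outcomes differ from those retained by δ SD. The mean of the whole arm is the retained mean plus w × δ. The retained-only contrast is therefore off by |w(active) − w(sham)| × δ.

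| Arm difference in withdrawal (assumed) | δ = 0.25 | δ = 0.5 | δ = 1.0 |
|---|---|---|---|
| 0 points | 0 | 0 | 0 |
| 10 points | 0.025 SD | 0.05 SD | 0.10 SD |
| 20 points | 0.05 SD | 0.10 SD | 0.20 SD |

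Direction: if withdrawn participants do worse and more leave sham, sham looks better than it is and the bias works against rTMS. If more leave the active arm, it favours rTMS.

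**The case against.** The best reply has five parts.

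- **Silence is not a statement.** A reader might infer that the article says no T.23 or T.24 outcome is taken after withdrawal. It does not. That follows only from the words used and from the absence of any continued-follow-up statement, and the detailed measures table and flow figures are not shown. This limits the point to what the rule means as written. It does not remove it, because the level of withdrawal is stated outright. If the full protocol continues follow-up, this section misdescribes it.
- **The triggers are narrow.** A reader might take it that any three missed sessions, or any adverse event, ends participation. The sessions must be consecutive, missed ones can be replaced, and only an event judged unsafe counts. This makes withdrawal rarer, at a rate nobody can state from the article.
- **The model uses partial data.** A reader might conclude that the analysis becomes one of adherent patients. A random-effects growth model can keep partial records under missing at random, and per-session binge counts add information up to withdrawal. This stands as mitigation. It does not supply the diary at T.23 or anything at T.24, it gives nothing after baseline for someone with no sessions, and missing at random is doubtful for non-adherence or a new drug.
- **CACE counts most withdrawn participants as compliers.** This is correct: one session is enough. The rule does not remove all non-compliers' data through mid-treatment withdrawals; the conflict lies with those who attended none.
- **The ITT sentence is loose wording.** Set against CACE, it may simply mean that receipt of treatment is ignored, and nothing in it excludes an allocated participant. That is fair; it needs rewording and does not show that anyone will be dropped.

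**Conclusion.** The point holds in a bounded form. The article states a rule that ends study participation for events after randomisation tied to adherence, new medication and harm, and it states no continued outcome collection. Followed as written, that rule conflicts with the ITT and CACE analyses promised in the same article.

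The size cannot be fixed from the documents. On assumed arm imbalances of 10 to 20 points and outcome differences of 0.25 to 1.0 SD, an observed-case contrast moves by 0.025 to 0.20 SD, in either direction; with equal withdrawal and the same outcome difference in both arms, it does not move. The planned growth model is not an observed-case contrast, so these figures illustrate the exposure and do not predict it.

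The power figures (0.82 falling to 0.78, 0.73 and 0.67) assume that withdrawn participants contribute nothing, use alpha 0.05 as in the sample size paragraph, and rest on the between-groups test that reproduces 60. Partial data would make the loss smaller.

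The documents do not support the claim that the trial will be biased, or that the bias would favour rTMS.

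**What to change.** Leave the listed criteria and the investigator's safety judgement exactly as they are, but label them discontinuation of rTMS. Then state that every randomised participant who still consents continues the diary, VAS and questionnaires at T.23 and T.24, omitting any procedure that is contraindicated or judged unsafe. The primary craving VAS is defined from T.3 to T.22, so the amendment should also say which assessment serves for someone no longer attending sessions.

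Reword ITT as all randomised participants analysed in their assigned arm regardless of sessions received.

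Cost: a short amendment with matching consent wording, and some effort to retain people who have stopped treatment. The T.23 and T.24 visits already exist, and the diary, VAS and questionnaires are self-completed.

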### Intervention

Following assessment, participants eligible for the study will undergo a preliminary fMRI, followed by 20 sessions of neuronavigated rTMS, one session per day, 3 days/week over approximately 7 weeks. Focal rTMS will be performed using a Neurosoft device and a ‘figure of eight’ coil. Brainscience Neuronavigation will be used to guide the placement of the coil to the target PFC region using a template MRI for all participants. The coil will be placed at a 45° angle to the mid-sagittal line to induce a posterior to anterior current in the underlying neural tissue. For the real treatment condition, stimulation will target the left DLPFC at 110 % of the resting motor threshold. Each session of 10 Hz stimulation will apply 1000 pulses to the left hemisphere, with a duty cycle of 5 s on and 55 s off, for a total stimulation time of 20 min. Sham rTMS treatment will be administered with the same TMS methodology used for real intervention, except for the fact that in the sham condition there is no actual magnetic stimulation. In order to mimic the cutaneous sensation and muscle twitching of rTMS without stimulating the brain, focal electrical stimulation will be used as a sham rTMS condition. To ensure treatment adherence, if rTMS sessions are missed, replacement sessions will be schedule within a week.

### Measures

Additional file 1: Table S1 describes the study measures and timeframe in details.

#### Diagnosis and eligibility measures

##### Anthropometric measures

Height and weight will be measured in triplicate using a stadiometer and a scale. Participants will be backwards and in a hospital gown. Hip-waist circumference and ratio will be measured in triplicate also.

##### Laboratory blood examination

Fasting blood samples will be obtained for a complete blood count, fasting glucose levels, fasting glucose/insulin ratio, TSH, and free thyroxine (T4). A urine pregnancy test will be collected if pregnant condition is possible (women in fertile age and not using a reliable contraceptive method).

##### Diagnostic interviews

Psychiatric diagnosis will be assessed with The Structured Clinical Interview (MINI 7.0). The interview comprises modules representing different groups of psychiatric disorders. In order to confirm BED diagnosis (DSM-5) and collect further information on ED psychopathology, The Eating Disorder Examination (EDE 17.0D) will also be applied. The EDE is a semi-structured diagnostic interview and the gold-standard instrument used in the diagnosis of eating disorders [58]. It has four subscales of symptoms severity (shape, weight and eating concern and dietary restrain) and a global score. In addition the number of binge eating episodes and days during the past month (or 28 days) is carefully assessed during the interview. Trained professionals will be conducting these interviews.

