#### Primary outcome measures

The primary outcomes of this study are: (1) the change in the number of BE episodes before and after study treatment (number of BE episodes at baseline subtracted from the number of BE episodes at the end of treatment), as measured by participants recording of binge episodes in the food diary during the previous 15 days to the baseline visit (first rTMS session, T.3) to the end of treatment visit (T.23); (2) the change in “urge to eat” (craving) as measured in a 10 cm VAS (from T3 to T22).

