#### Secondary outcome measures

Self report measuresA short and modified version (comprising 8 items) of the Food Craving Questionnaire-Trait (FCQ-T) [59]. The FCQ-T was translated and adapted to Brazilian Portuguese (publication in progress). This instrument investigates various aspects of food cravings across different time periods and situations.Binge Eating Scale (BES) [60]. BE severity will be examined using the BES, which is composed of 16 items and has been translated and validated to Portuguese Change in the total mean score from the baseline visit (T.3) to the end-of treatment evaluation (T.23) and 8-week follow up (T.24) will be compared between the two randomized groups.Three Eating Factor Questionnaire (TEF-Q) [61]. The reduced 21 item version (TEFQ-R21) [62], which has been translated and adapted to Brazilian Portuguese [63] will be used. Overall, the questionnaire evaluates the following aspects: eating cognitive restrain, emotional eating and control over eating.The Loss of Control over Eating Scale (LOCES) [64] is an instrument developed to investigate aspects associated with the loss of control over eating. The scale has been translated and validated to Brazilian Portuguese (publication in progress).UPPS Impulsive Behavior Scale [65] was originally developed with five factors and later reduced to four factors and 45-items [66]. These factors were divided as: a) urgency, tendency to experience strong impulses, b) lack of premeditation, tendency not to think about the consequences of an act before engaging in it, c) lack of perseverance, lack of the ability to stay focused on a task that can be boring or difficult, and d) sensation seeking, tendency to search for activities that are exciting, and openness to try new experiences. The scale is also available in Brazilian Portuguese [67].Depression Anxiety Stress Scales (DASS-21) is a 21-item self-report scale [68] developed to measure the negative emotional states of depression, anxiety and stress during the past week. Each item is rated using a 4-point severity/frequency scale according to the corresponding statement. DASS-21 is available in Brazilian Portuguese [69].Food diary. Participants will be instructed to register complete food intake in a food diary for seven consecutive days before the T.3, T.23 and T.24 visits, and to record BE episodes for 15 consecutive days before the same time points (T.3, T.23 and T.24).Body Shape Questionnaire (BSQ-34). The questionnaire has been validated in patients with eating disorders and includes assessments of body image. The questions related to body shape perception and range from 1 to 6. Higher scores on these scales indicate greater psychopathology. The questionnaire has been translated and validated to Brazilian Portuguese [70].The 12-item Short Form Health Survey (SF-12). This questionnaire measures health-related quality of life, subdivided in two scales – Physical Health Component Summary scales (PCS) and Mental Health Component Summary scales (MCS) [71]. It has been translated into Brazilian Portuguese [72].

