### Randomization

A simple randomization will be conducted with a 1:1 allocation. A randomization sequence list will be created using the website www.random.org, which offers true random numbers; such randomness comes from atmospheric noise, which for many purposes is better than the pseudo-random number algorithms typically used in computer program. Participants will be randomly assigned following simple randomization sequence to one of the two treatments. Group 1 for active rTMS and group 2 for sham rTMS. Patient allocation will be blinded to all participants and study staff, in exception to the professionals providing the rTMS treatment and one doctorate student, responsible for allocation concealment. The allocation sequence will be concealed and sequentially numbered in dark, sealed and stapled envelopes and locked in a key protected cabinet file. Allocation implementation will occur pre-intervention and between the T.2 and T.3 visits.

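### The first primary outcome is a raw change from one 15-day diary; adjusting for that diary count and for the 28-day EDE binge count already collected would be a nearly free, modest gain in precision

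*Protocol article*

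**What the plan says.** All references are to the protocol article.

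- **Primary outcome measures.** The binge-eating outcome is the "number of BE episodes at baseline subtracted from the number of BE episodes at the end of treatment". The baseline comes from "participants recording of binge episodes in the food diary during the previous 15 days to the baseline visit (first rTMS session, T.3"; the end point is T.23.
- **Secondary outcome measures, food diary item.** Patients are asked "to record BE episodes for 15 consecutive days before the same time points (T.3, T.23 and T.24". There is therefore only one diary count before treatment.
- **Diagnostic interviews.** The EDE has a diagnostic and descriptive purpose: "In order to confirm BED diagnosis (DSM-5) and collect further information on ED psychopathology, The Eating Disorder Examination (EDE 17.0D) will also be applied". It yields a second count of the same behaviour over a longer window: "In addition the number of binge eating episodes and days during the past month (or 28 days) is carefully assessed during the interview".
- **Randomization.** "Allocation implementation will occur pre-intervention and between the T.2 and T.3 visits".
- **Sample size and statistical analysis.** "Underlying both paradigms, it will be used growth modeling, which examines the development of individuals on one more outcome variables over the time". The sample-size inputs include "number of measurements through the follow-up = 3 and correlation among repeated measurements = 0.5". No covariate of any kind is named. The Bonferroni test level is 0.0015 for 32 outcomes.

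**The concern.** A raw change score carries the noise of both counts. When the two counts correlate 0.5, as the plan assumes, the change is no more precise than the end-of-treatment count alone, so the baseline buys nothing. Using the baseline as a covariate does better. A second baseline count can do better again, and here one is gathered anyway, over 28 days rather than 15.

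The EDE serves to confirm the diagnosis required for randomization, so it should precede allocation and be a valid baseline covariate. With 60 randomised patients and a test level of 0.0015, precision is scarce, and a gain that needs no new visit or measurement deserves a sentence in the plan.

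**Working it through.** **Inputs from the document.** Effect size f = 0.31; alpha 0.05 in the sample-size paragraph and 0.0015 for testing; target power 0.80; 2 groups; 3 measurements; correlation 0.5; 60 patients at 1:1, so 30 per arm.

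**Assumption.** The document gives no correlation between the EDE count and either diary count. I start from 0.5 and then vary it.

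**1. The plan's own sample size.** For a between-group repeated-measures test, lambda = f² × N × m / (1 + (m − 1) × rho), with 1 and N − 2 degrees of freedom. At N = 58, lambda = 0.0961 × 58 × 3 / 2 = 8.36 and power is 0.811. At N = 60, lambda = 8.65 and power is 0.824. The smallest even N reaching 0.80 is 58, so the planned 60 is reproduced to within two patients.

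**2. Residual variance for the T.23 comparison**, in units of the variance of one diary count. For two equal groups d = 2f = 0.62.

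- Raw change: 2(1 − 0.5) = 1.00
- Adjusted for the T.3 count: 1 − 0.5² = 0.75
- Adjusted for T.3 and EDE: 1 − R², where R² = (r_DY² + r_EY² − 2 r_DY r_EY r_DE) / (1 − r_DE²). Here D is the T.3 diary, E the EDE count and Y the T.23 diary. With all three at 0.5, R² = (0.25 + 0.25 − 0.25) / 0.75 = 0.333, leaving 0.667.

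**3. Power**, noncentral t, 30 per arm, d = 0.62:

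| Analysis | Residual variance | Alpha 0.05 | Alpha 0.0015 |
|---|---|---|---|
| Raw change | 1.00 | 0.656 | 0.190 |
| T.3 as covariate | 0.75 | 0.778 | 0.300 |
| T.3 and EDE as covariates | 0.667 | 0.824 | 0.357 |

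The whole step is about 17 points at either level. Of this, 12 points (alpha 0.05) or 11 points (alpha 0.0015) come from adjusting for T.3, which needs no EDE. The EDE's own share is 4.6 or 5.7 points. For 80% power at alpha 0.05, it lowers the requirement from 32 to 29 per arm.

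**4. How far the EDE share depends on the unknown correlations** (T.3 with T.23 held at 0.5):

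| EDE with T.23 | EDE with T.3 | Residual variance | Gain, alpha 0.05 | Gain, alpha 0.0015 |
|---|---|---|---|---|
| 0.3 | 0.6 | 0.750 | nil | nil |
| 0.4 | 0.8 | 0.750 | nil | nil |
| 0.3 | 0.3 | 0.725 | 1.3 points | 1.5 points |
| 0.5 | 0.5 | 0.667 | 4.6 points | 5.7 points |
| 0.57 | 0.57 | 0.629 | 6.7 points | 8.8 points |

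The value 0.57 is what a stable personal binge rate would imply if it produces 0.5 between 15-day counts and the EDE covers 28 days. Larger gains need the EDE to track the T.23 diary better than the adjacent T.3 diary (for example 0.6 against 0.5, residual variance 0.587), which is less plausible.

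**5. Where the EDE count enters matters.** If it is added to the raw change alone, the residual variance is 1 − (r_EY − r_DE)² in these units when T.3 and T.23 correlate 0.5. Under equal correlations that is 1.00: no gain. The same holds in a growth model in which arm predicts both intercept and slope, because T.3 is then an outcome and the arms' baseline means are free. The relative variance of the treatment effect goes from 1.00 to 1.016 and power from 65.6% to 64.9%. The gain appears only when the T.3 count is a covariate or the arms share a T.3 mean.

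**The case against.** The strongest reply is that this is silence, not a choice. The analysis section names no covariates and excludes none, and a condensed article may leave the covariate list to an analysis plan that is not shown. That stands. A reader might infer that the plan has discarded the EDE count or that the growth model cannot take it. Neither is supported, since such a model can carry it as a time-invariant predictor. What the article does fix is the outcome, as a raw change in a single short-window count.

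A second reply is that the raw-change test is not the stated analysis. The inference rests on growth modelling, and with a common baseline mean that model already reaches the residual variance of 0.75. This also stands. The article does not say how the baseline means are treated, so the 12-point step may or may not already be secured.

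Third, the EDE is a recalled interview count and the diary is a prospective record. The EDE also helps select patients, which may narrow its range and weaken its correlations, and its window may overlap the diary's. All of this pulls the gain downwards, possibly to nil.

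Finally, a reader might infer that the T.3 diary is compromised because its 15 days may extend past allocation. The document gives no route for that: participants are blinded and the count ends before the first session.

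**Conclusion.** The point holds as an optional improvement of low severity. The first primary outcome is defined as a raw change from one 15-day diary, and a 28-day EDE binge count collected for eligibility has no stated analysis role. At 30 per arm, d = 0.62 and correlation 0.5, T.3 adjustment is worth 12 points of power at alpha 0.05 and 11 at 0.0015, unless the growth model already delivers it. The EDE count is worth about 5 or 6 points more if it correlates 0.5 with both diary counts, with a plausible range of nil to about 9.

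It would be tempting to credit the EDE with the full 17 points; most of that belongs to the handling of T.3. That the EDE precedes allocation is an inference from its use for eligibility, because the visit table (Table S1) is not shown.

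**What to change.** Before unblinding, specify one of the following for the binge-eating outcome:

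- Analyse the T.23 diary count with the T.3 diary count and the pre-allocation EDE 28-day count as baseline covariates.
- In the Mplus growth model, set time zero at T.3, constrain the arms to a common T.3 mean (no path from arm to intercept), and let the EDE count predict intercept and slope.

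State the common-mean constraint explicitly; without it the second option gains nothing under equal correlations. Do not use the EDE count in place of the diary baseline or inside the change score, because instrument and window differ. Confirm from the visit schedule that the EDE is completed before allocation.

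The cost is one or two sentences and about one degree of freedom. In the nil-gain cases above, power falls by less than 0.1 point. No new data, visits or staff are needed.
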